## Primary Endpoint Analysis: Sample Size Selection

The sample size of the study was chosen based on a review of the literature for exploratory EEG studies of novel neurotechnologies. Utilizing a sample size of 20 for this initial study will allow us to best estimate effects sizes of critical measures to be examined in follow-up confirmatory studies.

## Eligibility of Subjects, Exclusions, Missing Data, and Removal of Subjects

All subjects responding to the advertisements are potential study candidates and will be screened for eligibility. Every effort will be made to ensure eligibility of the subjects prior to study enrollment. Subjects who do not meet all inclusion/exclusion criteria will not be enrolled or followed in the study. Subjects for whom no data was acquired due to technical failures or those that withdraw consent will be excluded from analysis. Subjects for whom only partial data was acquired will be included in all possible analysis.

# ADVERSE EVENT REPORTING

## Serious Adverse Events

A serious adverse event is any adverse event which occurs during the study visit

i. is life threatening; or

ii. results in permanent impairment of a body function or permanent damage to a body structure; or

iii. necessitates significant intervention, such as major surgery, to prevent permanent impairment of a body function or permanent damage to a body structure; or

iv. requires hospitalization or an extended hospital stay; or

v. results in moderate transient impairment of a body function or transient damage to a body structure; or

vi. requires intervention, such as medication or cardioversion to prevent permanent impairment of a body function or damage to a body structure.

Examples of serious adverse events include death, cardiac tamponade, myocardial infarction, stroke, and seizure.

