## Study Design

This is a non-randomized prospective experimental study.

Study Procedures are as follows:

1. Informed Consent
2. Eligibility Assessment
3. First EEG Recording
4. One week washout period
5. Second EEG Recording

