**SECOND STUDY VISIT**

The second study visit will be a replication of Part C of the first visit. At the conclusion of the visit, the subject will be provided financial compensation of $100 CAD for the study.

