## Adverse Events

An adverse event is any adverse event that results in minimal transient impairment of a body function or damage to a body structure or which does not require any intervention other than monitoring. Examples of an adverse event include skin reaction or headache at the locations where the Vielight Neuro Gamma device makes contact with the subject's skin.

A pre-existing condition should not be reported as an adverse event unless there has been a substantial change in severity that cannot be attributed to natural history.

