## Reporting

As this is a minimal-risk study, no serious adverse events are anticipated. However, any adverse events reported by subjects or observed by the study staff, during the course of the study visit procedures, will be recorded in the subjects CRF along with a brief description and any action taken. All adverse events determined by the principal investigator to be a potential result of study visit procedures, will be reported to the Institutional Review Board and the study sponsor.

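### Section 7.1 counts an event as serious only if it occurs during the study visit, and the protocol describes no planned adverse event question at visit 2 and no contact after session 2

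*Protocol*

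**What the plan says.** Four places in the protocol bear on this.

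- **Section 7.1 (Serious Adverse Events)** opens with "A serious adverse event is any adverse event which occurs during the study visit" and then lists six criteria, among them threat to life, lasting impairment and hospitalization. Its examples include stroke and seizure.
- **Section 7.2 (Adverse Events)** gives the lesser category: "An adverse event is any adverse event that results in minimal transient impairment of a body function or damage to a body structure", or one that needs nothing beyond monitoring. It states no time limit.
- **Section 7.3 (Reporting)** says that "any adverse events reported by subjects or observed by the study staff, during the course of the study visit procedures, will be recorded" in the CRF. On onward reporting to the IRB and sponsor it says: "All adverse events determined by the principal investigator to be a potential result of study visit procedures, will be reported". It also states: "As this is a minimal-risk study, no serious adverse events are anticipated".
- **Section 4.3 (Study Visit Procedures)** says of visit 2: "The second study visit will be a replication of Part C of the first visit". Part C covers seating, subject details, cap placement and three EEG recordings. It lists no question about events since visit 1. Visit 2 ends with payment of the subject.

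The sessions are separated by the step listed under Study Design as "One week washout period".

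**The concern.** The time limit in 7.1 is part of the definition, so it decides what a serious event is and not merely when staff look for one. A serious event in the washout week or after session 2 fails the definition however grave it is. It does not readily fit 7.2 either, because that section describes minor, self-limiting events. Such an event falls between the two categories.

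The subjects are aged 60 or older. At stake are the correct classification of the most important events that could occur and a planned means of hearing about later ones. Any description of how the active and sham sessions were tolerated would depend on both.

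**Working it through.** The protocol states no safety figure, event rate or power for safety, so there is nothing to reproduce. The check compares the passages and then sizes the observation window.

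**1. Time limits side by side**

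| Section | What it governs | Time limit stated |
| --- | --- | --- |
| 7.1 | Definition of a serious event | Occurrence during the visit |
| 7.2 | Definition of a non-serious event | None |
| 7.3, recording | Entry in the CRF | Reported or observed during visit procedures |
| 7.3, onward reporting | Notice to IRB and sponsor | None; filtered by the investigator's causality judgement |

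The less grave category is thus open in time and the graver one closed. The limit in 7.3 can attach to when an event is reported or observed rather than when it began, so it does not settle the matter.

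**2. The limit against the criteria in 7.1.** Hospitalization, a prolonged stay and permanent impairment normally become known after a subject has left. Read literally, the opening sentence of 7.1 excludes much of what its own list is meant to catch.

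**3. Routes of capture by period**

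- *During either visit:* observation by staff or report by the subject.
- *Washout week:* only if the subject volunteers the event at visit 2. It can then be recorded under 7.3, but it still cannot be serious under 7.1.
- *After session 2:* no route is described.

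Capture therefore differs by session. The Synopsis calls the crossover randomized, while Study Design calls the study non-randomized. If the order is not balanced, the difference in capture would fall unequally on active and sham.

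**4. Size of the observation window.** Inputs from section 4.3 are recordings of 10, 20 and 10 minutes per visit, two visits and a one-week gap.

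- Recording per visit: 10 + 20 + 10 = 40 min; over two visits, 80 min.
- Gap: 7 × 24 × 60 = 10,080 min.
- Share observed from session 1 to the end of session 2: 80 / (10,080 + 80) = 80 / 10,160 = 0.8%.
- Total visit length is not stated. Assuming 60 min per visit, 120 / 10,200 = 1.2%; assuming 180 min, 360 / 10,440 = 3.4%.
- After session 2: zero.

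**5. What incomplete capture would do (assumed rates only).** With 20 subjects, a true per-subject event rate p and a captured fraction f, the chance of seeing at least one event is 1 − (1 − p·f)^20. Take p = 5%:

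- f = 100%: 1 − 0.95^20 = 64%
- f = 75%: 1 − 0.9625^20 = 53%
- f = 50%: 1 − 0.975^20 = 40%
- f = 25%: 1 − 0.9875^20 = 22%

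Neither p nor f comes from the protocol. The figures show direction and scale and do not estimate what this trial would miss.

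**The case against.** The strongest reply is that this is a short exploratory EEG study with no safety objective or endpoint, and that the text is less restrictive than it looks. Much of that is right, and it rules out several stronger readings.

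- *A reader might infer that no adverse event counts unless it occurs during a visit.* Only 7.1 says so. Section 7.2 has no limit, and the limit in 7.3 can mean time of reporting. A washout-week event mentioned at visit 2 can be recorded. Capture between visits is unsolicited, not nil.
- *A reader might infer that a serious event judged unrelated never reaches the sponsor.* The documents do not support this. Section 7.3 puts recorded events in the CRF whatever their cause, section 8.6 has the sponsor monitor source-to-CRF verification, and section 8.2 requires the sponsor to verify the data. What is missing is a stated reporting route that does not depend on causality.
- *A reader might infer that the trial fails to support its minimal-risk statement.* That statement is a premise for expecting no serious events, and the trial does not set out to test it. Zero events in 20 subjects gives a one-sided 95% upper limit of 1 − 0.05^(1/20) = 13.9% even with complete capture. That is a limit of the sample size, which a longer window would not change.
- *The 0.8% share counts clock time.* It does not say that 99% of events are missed, since nothing in the protocol suggests that every hour after a session carries equal risk.
- *The CRF and consent pages are not at hand.* A prompt or an instruction to report later problems may exist there.

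None of this repairs 7.1. A CRF prompt could bring in a later event, but the definition would still deny that it was serious.

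**Conclusion.** The concern holds for the definition in 7.1 and for the lack of any described ascertainment after the visits. As worded, a serious event in the washout week or after session 2 is not a serious adverse event, which sits badly with the open-ended 7.2 and with the criteria in 7.1. Capture between visits depends on what subjects volunteer, and after session 2 no route is planned.

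The consequence is confined to safety classification and reporting; the primary EEG comparison does not change. The number of events that might be missed cannot be estimated from the protocol. The conclusion on 7.1 rests on the plain wording alone. The conclusion on ascertainment assumes that no prompt exists in the CRF or consent material. The change is worth making before the study starts because it costs very little.

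**What to change.** 1. **Section 7.1:** strike the last five words of the opening sentence so that it runs directly into the six criteria. This removes the visit limit and leaves a sentence that reads correctly.
2. **Sections 7.1 to 7.3:** state one collection period that governs all three, from the start of visit 1 study procedures to a fixed time after session 2. It should not begin at device placement. Cap fitting, saline and the 10-minute baseline come before that and are now covered by 7.3 as visit procedures. Say in 7.3 that the period refers to onset.
3. **Section 4.3 and the CRF:** add one open adverse event question at the start of visit 2, with the answer attributed to the session 1 condition.
4. **Preferably**, add one brief phone or e-mail contact after session 2 with the same look-back, so that both sessions are ascertained equally. With a one-week look-back and visit 1 at recruitment, the last subject would be contacted at 4 + 1 + 1 = 6 weeks. That matches the planned completion in section 8.1, without slack.
5. **Preferably**, state in 7.3 a reporting route for serious events that does not depend only on the investigator's causality judgement.

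The cost is one CRF line, one short contact per subject by existing staff, and slightly more events to record.

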## Adverse Events

An adverse event is any adverse event that results in minimal transient impairment of a body function or damage to a body structure or which does not require any intervention other than monitoring. Examples of an adverse event include skin reaction or headache at the locations where the Vielight Neuro Gamma device makes contact with the subject's skin.

A pre-existing condition should not be reported as an adverse event unless there has been a substantial change in severity that cannot be attributed to natural history.

## Reporting

As this is a minimal-risk study, no serious adverse events are anticipated. However, any adverse events reported by subjects or observed by the study staff, during the course of the study visit procedures, will be recorded in the subjects CRF along with a brief description and any action taken. All adverse events determined by the principal investigator to be a potential result of study visit procedures, will be reported to the Institutional Review Board and the study sponsor.

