- Study staff will record any relevant subject details (physical characteristics and demographics) in the Case Report Form. These include but are not limited to: the Subject’s date of birth (YYYY-MM-DD), sex, weight, height, etc.
- Study staff will place the saline-rinsed EEG electrode cap on the subject and may apply additional saline to individual electrode locations in order to ensure good conductivity
- Once the electrode cap is producing reliable readings, the subject will be asked to remain still and quiet with their eyes closed for an initial 10 min Rest-EEG recording
- At the completion of the 10 min recording, study staff will then place the Vielight Neuro Gamma device or Sham device on the subject, as shown in Figure 2 above.
- Study staff may then re-apply additional saline to individual electrode locations in order to ensure good conductivity
- Once the electrode cap is producing reliable readings, the subject will be asked again to remain still and quiet with their eyes closed for a 20 min Rest-EEG recording
- At the completion of the 20 min recording, study staff will then remove the Vielight Neuro Gamma device or Sham device and again re-apply additional saline to individual electrode locations in order to ensure good conductivity
- Once the electrode cap is producing reliable readings, the subject will be asked to remain still and quiet with their eyes closed for a final 10 min Rest-EEG recording

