## Device Safety

Vielight Neuro Gamma: The controller houses three 1.5V NiMH batteries (1900 mAh each) and the controlling electronics for the Neuro Gamma. Both the Headset and Nasal Applicator are connected to the controller with connectors that prevent them from being incorrectly inserted. A single button initiates a software controlled 20-minute therapy – automatically timed but can be discontinued by pressing the button a second time. The maximum power output density to the nasal mucosa is 25 mW/cm^2^ with a 50% duty cycle (total energy delivered per session = 15 J). The maximum power output density to the scalp is 100 mW/cm^2^ with a 50% duty cycle for the posterior band LEDs and 100 mW/cm^2^ with a 50% duty cycle for the anterior band LED (total energy delivered per session = 225 J). All LEDs are well under the exposure limits established by IEC 62471:2006 - *Photobiological safety of lamps and lamp systems*..

BrainMaster Discovery 20 System: The BrainMaster Device does not produce any electro-magnetic fields and does not interfere with the operability of other devices The unit is entirely powered by the USB interface, eliminating the need for batteries, while maintaining subject safety.

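### No step at either visit asks about symptoms, although subjects are kept quiet throughout device exposure, so subjective events such as headache may be under-recorded

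*Protocol*

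**What the plan says.** Protocol section 7.3 (Reporting) describes how adverse events reach the case report form (CRF). It covers "any adverse events reported by subjects or observed by the study staff, during the course of the study visit procedures", noted with a brief description and any action taken.

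Section 7.2 (Adverse Events) gives two examples: "Examples of an adverse event include skin reaction or headache at the locations where the Vielight Neuro Gamma device makes contact" with the skin.

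Section 4.3, Part C, sets out the session step by step. After an initial 10-minute resting recording the active or sham device is fitted, and "the subject will be asked again to remain still and quiet with their eyes closed for a 20 min Rest-EEG recording". Section 5.2 (Device Safety) gives the length of exposure: "A single button initiates a software controlled 20-minute therapy". When that recording ends, "study staff will then remove the Vielight Neuro Gamma device or Sham device and again re-apply additional saline to individual electrode locations". The last listed step is that "the subject will be asked to remain still and quiet with their eyes closed for a final 10 min Rest-EEG recording".

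For the other session, "The second study visit will be a replication of Part C of the first visit", followed by payment of the subject.

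**The concern.** Part C is written in detail, down to each re-wetting of the electrodes, yet no step asks the subject about symptoms, either after the device comes off or at the end. The one stated route to the CRF is a report by the subject or an observation by staff. Staff can see a skin reaction. They cannot see a headache, so recording one depends on the subject mentioning it. The subject has been asked to be quiet for the whole exposure, and the session closes with another quiet period.

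Two things are at stake. First, the absolute count of subjective events may be too low, and a zero would be hard to read. Second, each subject receives both active and sham, so the design could yield a within-subject description of tolerability for almost nothing. Section 6.2 says the study is meant to inform follow-up confirmatory studies, and such a description would be useful there. If asking is left to individual staff, it may differ between subjects and between sessions.

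**Working it through.** This is mainly a check of the text. The Protocol states no adverse event rate, safety endpoint or capture rate, so there is no figure to reproduce.

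**Step 1: when the subject is asked to be quiet (section 4.3, Part C).** The recordings last 10 + 20 + 10 = 40 minutes per session, all under the same instruction. The 20-minute middle recording equals the 20-minute device session in section 5.2, so the instruction covers the whole exposure.

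**Step 2: when the subject can speak.** The instruction is tied to the recordings. It does not apply while the device is fitted or removed, while saline is re-applied, or after the last recording. Staff are with the subject when the device is fitted and removed.

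**Step 3: whether anyone is told to ask.** Going through Parts A to C of the first visit and the second visit, which repeats Part C, there is no symptom question, checklist or end-of-session check. Section 7.3 neither requires nor forbids one.

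**Step 4: which example events depend on being asked.** Of the two in section 7.2, skin reaction is visible at device removal and headache is not.

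**Step 5: illustration of the possible size.** The number of subjects, n = 20, is from section 4.1. Two quantities are assumptions that the Protocol does not give: *p*, the true proportion of subjects with a headache in a session, and *c*, the probability that a headache is recorded when nobody asks. With independent subjects:

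expected number recorded = 20·p·c, and P(none recorded) = (1 − p·c)^20.

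| p (assumed) | c = 1: expected | c = 1: P(none) | c = 0.5: expected | c = 0.5: P(none) |
|---|---|---|---|---|
| 5% | 1.0 | 0.95^20 = 0.358 | 0.5 | 0.975^20 = 0.603 |
| 10% | 2.0 | 0.90^20 = 0.122 | 1.0 | 0.95^20 = 0.358 |
| 20% | 4.0 | 0.80^20 = 0.012 | 2.0 | 0.90^20 = 0.122 |

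**Step 6: what a zero would mean.** With 0 events in 20 subjects, the exact one-sided 95% upper bound on the *recorded* rate is 1 − 0.05^(1/20) = 0.139. That figure reflects only n = 20 and holds even if every event is captured. To bound the *true* rate, divide by c: 0.139/0.7 = 0.199 and 0.139/0.5 = 0.278. The values 0.7 and 0.5 are again assumed, and all of the widening beyond 13.9% comes from them.

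The direction follows whenever c is below 1. The size cannot be taken from the Protocol.

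**The case against.** The strongest reply is that the text does not say events are recorded only if volunteered. An answer to a question is also a report by the subject, section 7.3 does not stop staff from asking, and the CRF is not shown. Subjects are in direct contact with staff as soon as the exposure ends, with no request for silence then, and at the second visit contact continues until payment. A headache can be mentioned a few minutes late. Nothing tells subjects to withhold discomfort. The trial also has no safety or tolerability endpoint, and the capture rates in the illustration are assumptions.

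Most of this stands. It rules out saying that subjects are never asked, or that headache is in fact under-counted. What it leaves is that asking is not scheduled. If staff do ask, nothing makes the wording or timing the same across subjects and sessions. The lack of a safety endpoint lowers the priority of the point, but section 7 still commits the trial to recording these events.

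**Conclusion.** The point holds as a gap in the visit procedure: neither session schedules an inquiry about symptoms, subjects are kept quiet throughout exposure, and one of the two example events is invisible to staff. Subjective events may be under-recorded, and a low or zero count could not separate absence of symptoms from absence of a question. The size of the loss is unknown. The illustrated changes, such as 0.122 to 0.358 at p = 10%, rest on assumed values of *p* and *c*.

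A reader might go further in three ways that the Protocol does not support.

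- **Active-versus-sham bias.** The procedure is the same in both sessions. Incomplete capture lowers the counts and the information they carry, but nothing shows that it favours either condition.
- **An unsupported minimal-risk claim.** Section 7.3 uses minimal risk as the premise for anticipating no serious events. It is not a conclusion that the trial sets out to establish.
- **Filtering of headaches as natural history.** The clause in section 7.2 reads "A pre-existing condition should not be reported as an adverse event unless there has been a substantial change in severity". It concerns pre-existing conditions. A new headache at a contact site is that section's own example of an adverse event and is not excluded.

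This is a cheap improvement in safety capture and does not affect the EEG endpoint.

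**What to change.** Add one last step to Part C, after the final 10-minute recording, so that it applies at both visits:

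- one scripted open question on how the subject felt during the session;
- specific questions on headache and on skin or nasal discomfort at the contact sites;
- for each symptom, the phase of onset (before, during or after the device) and its severity, entered in the CRF.

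The wording should be identical in the two sessions, and the questions should be asked while subject and staff are still blinded. Report the answers by active and sham session.

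Because the questions follow the last recording, the EEG data are unaffected and the quiet instruction during recordings need not change.

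The cost is one scripted CRF page and about one minute per session with existing staff. The downside is that direct questions will bring in more minor events under both conditions, so the counts should be read as an active-versus-sham contrast and not set against trials that did not ask.
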